### Data management and monitoring

#### Data recording

The evaluators responsible for recording the subjects' CRF will undergo standardized training before the experiment to ensure clear and standardized recording methods.

#### Data audit

At the end of each subject's treatment, the researchers will submit the CRF, Informed Consent Form, and pelvic floor sEMG report to the principal researcher of the unit for review and approval within 3 working days.

#### Data entry

To protect the privacy of the subjects, the collected data will be stored on restricted-access computers. The passwords will be set by two independent researchers who are not directly involved in the study. They will be responsible for entering and verifying all information and data into the computer to ensure data accuracy.

#### Data monitoring

The Medical Ethics Committee of the medical institution will regularly review and track the trial data and progress. All data related to this study will be archived and stored by the participating research hospital from the date of study completion.

### Statistical method

#### Sample size

The sample size was calculated using the PASS 15.0 software. The PFM function will be analyzed by a combination of parameters in the sEMG. According to a previous study [10], the contractility of the slow-twitch fibres in PFM function is the main urinary control factor. Therefore, the change in mean amplitude (μV) of the sEMG during the 10-s tonic contraction phase, which represents the contractility of the slow-twitch fibres, was selected for calculation. Based on pilot study data, the mean ± standard deviation (SD) is 4.1 ± 2.7 μV in the acupuncture group and 1.9 ± 1.6 μV in the SA group. 32 cases will be required in each group (α = 0.05, 1–β = 0.90). Taking into account the 15% dropout rate, 38 cases per group were required. Therefore, an optimal sample size of 76 cases will be required.

#### Data analysis

All data will be analyzed using IBM SPSS Statistics (v26.0; IBM Corp, Armonk, NY, USA). The analysis will be conducted according to the intention-to-treat (ITT) principle, including all randomized participants. Safety analyses will be performed on the safety set, which includes all participants who received acupuncture. For both primary and secondary outcomes, missing data will be handled using generalized estimating equations (GEE), which provide valid statistical inference under the assumption of missing at random (MAR) without the need for explicit imputation. If the overall proportion of missing data exceeds 10%, sensitivity analyses will be performed to assess the robustness of the results to the missing data assumption. Missing data for safety outcomes will not be imputed.

Continuous variables will be presented as mean ± standard deviation (SD) if normally distributed, or as median (interquartile range, IQR) otherwise. Categorical variables will be summarized as frequencies and percentages. Baseline demographic and clinical characteristics will be compared using the chi-square test or Fisher's exact test for categorical variables, and independent-samples *t*-tests or Mann-Whitney U tests for continuous variables, as appropriate.

For repeated measurements obtained at three time points (T_0_, T_1_, and T_2_), GEE models will be used as the primary analytical approach to account for within-subject correlations. The models will include group, time, and group-by-time interaction terms, with an appropriate working correlation structure selected based on model fit and data characteristics. The group-by-time interaction will be examined first; if significant, simple effects analyses will be conducted, otherwise main effects will be interpreted. Multiple comparisons will be adjusted using the Bonferroni correction.

All adverse events (AEs) and serious adverse events (SAEs) will be listed. AEs will be classified as acupuncture-related or non-acupuncture-related events. The incidence of AEs will be summarized as the number and percentage of participants in each group and compared using Fisher's exact test. Given the exploratory nature of safety analyses, *P-*value will not be adjusted for multiple comparisons.

Effect sizes along with their 95% confidence intervals (CIs) will be reported. All statistical tests will be two-sided, and a *P* value <0.05 will be considered statistically significant.

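### The plan states without condition that GEE is valid under MAR; for unweighted GEE with a data-chosen working correlation, that holds only approximately and only if the covariance structure is close to correct

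*Protocol article*

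**What the plan says.** The Data analysis section commits to an analysis of everyone randomised: "The analysis will be conducted according to the intention-to-treat (ITT) principle, including all randomized participants". Missing primary and secondary outcome data are to be dealt with by GEE, "which provide valid statistical inference under the assumption of missing at random (MAR) without the need for explicit imputation". On the model it says: "The models will include group, time, and group-by-time interaction terms", "with an appropriate working correlation structure selected based on model fit and data characteristics". No inverse-probability weights, multiple imputation or likelihood-based model is named.

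There is one safeguard: "If the overall proportion of missing data exceeds 10%, sensitivity analyses will be performed". The method of those analyses is not given. The Sample size section expects some loss: "Taking into account the 15% dropout rate", the requirement rises from 32 to 38 per group.

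**The concern.** Ordinary GEE solves unweighted estimating equations on the observations that are present. Those equations have mean zero in general only if the chance of being observed does not depend on outcomes, given the model covariates. Here the covariates are only group and time. If the chance of a T2 reading depends on the T1 reading already observed, the data are MAR but that guarantee is lost.

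For a continuous outcome there is a partial rescue. When the working covariance matches the true one, GEE nearly coincides with likelihood-based generalised least squares and uses T0 and T1 to correct for selective loss of T2. Validity under MAR is therefore conditional. The plan states it unconditionally and does not fix the structure on which it depends.

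At stake is the T2 contrast between acupuncture and sham. A selective loss that differs by arm could shift it, and the report would still carry the plan's assurance of validity.

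**Working it through.** **The plan's own figure.** Inputs from the Sample size section: change 4.1 (SD 2.7) versus 1.9 (SD 1.6) μV, difference 2.2, two-sided α 0.05, power 0.90. With SD 2.7 in both arms, n = 2 × (1.960 + 1.282)² × 2.7² / 2.2² = 2 × 10.507 × 7.29 / 4.84 = 31.7, so 32 per arm; 32 / 0.85 = 37.6, so 38 per arm and 76 in total. The plan's figure reproduces and this point does not change it. The 2.2 μV is the yardstick below.

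**Why the working correlation matters.** The model with group, time and their interaction has one mean per group and time. Under independence, GEE estimates each by the mean of the observed values. If T0 and T1 are complete and T2 is missing for women with low T1, the T2 mean in that arm is biased by

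ρ × SD × (mean of standardised T1 among those observed).

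If the lowest fraction p on T1 are all lost, the last factor is φ(z_p)/(1 − p): 0.274 at p = 0.15, 0.195 at 0.10 and 0.109 at 0.05. The bias in the contrast is the difference between arms.

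The documents give no raw SD or correlation. I assume ρ of 0.7 to 0.8 and set the raw SD so that the change SD is 2.22 (root mean square of 2.7 and 1.6) or 2.7: SD = change SD / √(2(1 − ρ)), which is 2.87 to 4.27 μV, so ρ × SD is 2.01 to 3.42 μV.

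| T2 loss, arm 1 / arm 2 | Formula, independence (μV) | Simulation, independence (μV) |
|---|---|---|
| 15% / 0% | 0.55 to 0.94 | 0.45 to 0.78 |
| 15% / 10% or 10% / 5% | 0.16 to 0.30 | 0.12 to 0.23 |
| 5% / 0% | 0.22 to 0.37 | 0.15 to 0.30 |
| equal | 0 | about 0 |

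The simulation had 38 per arm, no true effect, and 1,000 trials per setting. With an exchangeable working correlation the bias was at most 0.034 μV at every split. As shares of 2.2 μV, the independence results are 0.45/2.2 = 20% to 0.78/2.2 = 35% at 15%/0%, and 0.12/2.2 = 5% to 0.23/2.2 = 10% at the two modest splits.

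**Large-sample check** (100,000 per arm, true contrast 2.2 μV; assumed SD 4 μV, ρ 0.5 or 0.8, about 15 to 17% of T2 missing; Monte Carlo error about 0.02):

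- Completely random missingness, or MAR in the same direction in both arms: bias about zero for every structure.
- MAR in the acupuncture arm, completely random in sham: independence +0.37 to +0.86; other structures about 0 to +0.30.
- MAR in opposite directions by arm: independence +0.76 to +1.73. Exchangeable or AR(1) gave +0.02 to +0.10 with equal SDs, but +0.34 to +0.63 when the T2 SD was 1.4 times the others. Unstructured working correlation gave +0.08 to +0.46.

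So a sensible correlation removes most of the bias when the variance is also constant, and only part of it when it is not.

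**With the pilot SDs by arm** (2.7 and 1.6; baseline SD 3 to 6 μV and T1–T2 change correlation 0.5 to 0.8 assumed), 15%/0% gave +0.23 to +1.11 μV under independence and within about ±0.22 under the other structures. With 15% lost in both arms the bias was 0.16 μV or less.

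**The case against.** The strongest case on the other side has four parts.

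1. *The structure is unlikely to be independence.* The plan uses GEE because readings on one woman are correlated and will choose the structure by fit. At a correlation of 0.7 or 0.8, independence is the least natural choice. This stands as to likelihood, but the text does not exclude it.

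2. *The 15% versus 0% split is assumed.* The plan gives 15% with no split by arm. This stands: that split is a worst case.

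3. *The design limits exposure.* Envelopes are opened after baseline assessment, treatment is one 10-minute session, and T2 follows 10 minutes later. Losing T2 after an observed T1 requires withdrawal or a failed recording within minutes. This stands, and it is the main reason for moderate severity. If the loss were driven by discomfort that no model variable captures, the data would not be MAR and a mixed model would not cure it either.

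4. *Sensitivity analyses are promised above 10% missing.* The planned 15% would trigger them, and their method may properly be left to an analysis plan. This mitigates in part. At 10% or less, the result rests on the incorrect sentence alone.

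A reader might infer that GEE requires completely random missingness, or that the T2 effect will be off by a quarter to a third. The documents support neither. Exchangeable GEE was close to unbiased under MAR in the equal-variance settings, and the large figures need independence together with a dropout split that the protocol does not state.

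**Conclusion.** The validity statement is wrong as written, and nothing else in the protocol repairs it. It concerns the primary analysis and is an assertion, so it is not a detail left to an analysis plan.

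The practical effect is probably small. Bias is near zero with a near-correct covariance or similar dropout in both arms. Under independence it is about 0.1 to 0.3 μV for modest arm imbalance and about 0.5 to 0.8 μV of 2.2 μV in the assumed worst case. More extreme assumptions, such as opposite dropout directions by arm or unequal variances, give larger values. All sizes depend on SDs, correlations and dropout mechanisms that are not in the documents, so they show direction and order of magnitude only. This should be fixed before analysis, but it does not by itself undermine the trial.

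A separate, minor point: the uncorrected robust 2-df Wald test of the interaction rejects about 6.3 to 6.7% of the time under the null at 38 to 32 per arm, against a nominal 5%. That is a small-sample matter and has no bearing on MAR.

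**What to change.** Delete the unconditional MAR statement, then do one of the following.

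(a) Make a likelihood-based mixed model for repeated measures with unstructured covariance the primary analysis (SPSS MIXED, in the software already named), and keep GEE as a sensitivity analysis.

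(b) Keep GEE as primary with a pre-specified non-independence working correlation. State that its validity is guaranteed for missingness that is completely random or depends on model covariates, and is approximate under MAR only if the covariance structure is near correct. Add one named MAR-valid analysis, either multiple imputation or the mixed model, and run it at any level of missingness, not only above 10%.

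The cost is wording and a few lines of code; sample size and data collection are unchanged. The drawback of (a) is that the mixed model assumes approximate normality, which is a reason to retain GEE alongside it.

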### Outcomes

#### The primary outcome

Mean amplitude during the 10-s tonic contraction phase.

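### The trial is sized on a change in amplitude, but the primary outcome is a level and no change or baseline-adjusted contrast is named as the between-group estimate, so the steps after the interaction test have no established power

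*Protocol article*

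**What the plan says.** All places are in the protocol article.

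- **The primary outcome:** "Mean amplitude during the 10-s tonic contraction phase". This is a level; neither a change nor a time point is named. The abstract (Methods) gives it as the difference in mean amplitude between the two groups, again a level.
- **Sample size:** the quantity used is "the change in mean amplitude (μV) of the sEMG during the 10-s tonic contraction phase", with pilot values of "4.1 ± 2.7 μV in the acupuncture group and 1.9 ± 1.6 μV in the SA group". The plan asks for 32 women per group at α = 0.05 and 90% power, and 38 per group after 15% dropout. The time point of the change is not given.
- **Data analysis:** GEE on the three time points T0, T1 and T2. "The models will include group, time, and group-by-time interaction terms"; no baseline covariate is listed. The interaction is looked at first. If it is significant, simple effects follow; if not, main effects are interpreted. "Multiple comparisons will be adjusted using the Bonferroni correction", without a count of the comparisons. "All statistical tests will be two-sided".

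The document gives no SD of the levels and no within-woman correlation.

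**The concern.** A change score removes the stable differences in amplitude between women, and a level keeps them. The SDs of 2.7 and 1.6 μV therefore say nothing direct about the precision of a comparison of levels at T1 or T2.

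The planned sequence can end at either of two comparisons that were not sized:

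- **Simple effects.** Read in the usual way, these are group differences in raw level at each time.
- **Main effect of group.** As usually computed, this averages over all three times. T0 is measured before allocation is revealed, so no treatment effect can exist there, and the average dilutes whatever effect exists later.

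The plan promises effect sizes with 95% confidence intervals. A two-degree-of-freedom interaction P value does not supply one, so the reported estimate would come from one of these later steps. At stake is whether that estimate has the precision the sample size section implies.

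**Working it through.** **Inputs.** From Sample size: difference 4.1 − 1.9 = 2.2 μV; change SDs 2.7 and 1.6; n = 32 per group; two-sided α = 0.05. Assumed: within-woman correlation ρ, common to all pairs of times, and equal variance at each time.

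**The plan's own figure.** With SD 2.7 in both arms, n = 2 × 2.7² × (1.960 + 1.282)² / 2.2² = 31.7, so 32; and 32 / 0.85 = 37.6, so 38. Both figures reproduce (normal approximation). With the two stated SDs, n = (2.7² + 1.6²) × 10.51 / 4.84 = 21.4, so 22. The 32 thus carries some reserve. Both SD bases are used below: 2.7, and the root mean square √((2.7² + 1.6²)/2) = 2.22.

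**Formulas** (S = SD of change; power = Φ(effect/SE − 1.96))

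- Difference in change: SE = S√(2/32). Power is 90% (S = 2.7) or 98% (S = 2.22) at any ρ.
- Raw level at one time: level SD = S/√(2(1 − ρ)).
- Baseline-adjusted: SD = level SD × √(1 − ρ²) = S√((1 + ρ)/2).
- Group main effect over T0–T2, with 2.2 μV at both T1 and T2: effect = (0 + 2.2 + 2.2)/3 = 1.47 μV; variance of a woman's mean = level SD² × (1 + 2ρ)/3.

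**Example, ρ = 0.8, S = 2.7.** Level SD = 2.7/0.632 = 4.27; SE = 4.27 × 0.25 = 1.07; 2.2/1.07 − 1.96 = 0.10; power 54%. Adjusted: SD = 2.7 × √0.9 = 2.56; SE = 0.64; power 93%. Main effect: SE = √(4.27² × 2.6/3 × 2/32) = 0.99; 1.47/0.99 − 1.96 = −0.48; power 31%.

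| Contrast, 32 per group | S | ρ = 0.5 | 0.7 | 0.8 | 0.9 |
|---|---|---|---|---|---|
| Raw level, T1 or T2 | 2.22 | 98% | 87% | 71% | 43% |
| Raw level, T1 or T2 | 2.7 | 90% | 71% | 54% | 31% |
| Raw level, Bonferroni for 2 | 2.7 | 85% | 61% | 43% | 22% |
| Group main effect over T0–T2 | 2.7 | 76% | 47% | 31% | 17% |
| Baseline-adjusted | 2.7 | 96% | 94% | 93% | 92% |

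**Interaction (2 df).** Under these assumptions the covariance of the two change contrasts is S² × (2/32), with correlation 0.5, so ρ drops out. With S = 2.7, power is 93% for an effect of 2.2 at both times, or at one time only, and 84% for 2.2 at one and 1.1 at the other. With S = 2.22 it is 99% and 95%.

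**Where the raw level test crosses 90%.** It needs a level SD of at most 2.2 / (3.24 × 0.25) = 2.71. With S = 2.22, ρ = 1 − 2.22²/(2 × 2.71²), about two thirds. With S = 2.7 the crossing is at ρ of about 0.5. Below ρ = 0.5 a level comparison is more precise than a change comparison.

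**The case against.** A reader might infer that the planned analysis ignores baseline, or that the trial is underpowered. The documents support neither.

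- **The first test uses T0.** With T0 among the responses, the group-by-time interaction is the between-group difference in change, which is the quantity that was sized, and it keeps roughly the stated power. This stands fully. The fallback main effect is reached only when that test is not significant.
- **The contrast is not written down.** Simple effects could mean groups at each time or times within group. Comparing levels between groups is the usual reading and the one that matches the abstract's outcome, but it is an inference. An analysis plan that is not shown might settle it. That does not remove the mismatch between the outcome definition and the sizing variable, which is in the protocol article itself.
- **The loss depends on ρ.** Nothing in the document shows that ρ is high. At 0.5 or below there is no loss.
- **The table is illustrative.** Unequal change SDs do not fit one ρ with equal variances: at a level SD of 4.96 they imply about 0.85 and 0.95.
- **Bonferroni.** That T0 is counted in the family is possible, but the text does not say so.
- **Validity.** Under randomisation an unadjusted comparison is unbiased. The issue is precision and clarity, not bias.

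**Conclusion.** The point holds as a mismatch and an unfixed primary contrast. The sizing variable is a change, the defined outcome is a level, and the analysis names neither a change nor a baseline-adjusted difference, nor a time point, as the between-group estimate. The sample size section supports the interaction test. It does not establish power for a level-based simple effect or for a main effect averaged over T0.

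If ρ is about 0.8, a level comparison has 54–71% power; if ρ is 0.5, it has 90–98%. The main-effect fallback is weaker at each ρ because a 2.2 μV effect shrinks by one third. These figures assume a common ρ, equal variances, and an effect of 2.2 μV at the time tested (at both T1 and T2 for the main effect). A power failure is therefore possible but not demonstrated. Baseline adjustment or a change contrast would hold the stated 90% at every ρ considered, using data already collected. The contrast should be settled before the data are analysed.

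**What to change.** 1. State the primary between-group estimate as either the T0-adjusted difference or the difference in change from T0 (the interaction contrast), at one time point that the sponsor names, with its 95% confidence interval. The document gives reasons for both T1 and T2 and ranks neither, so the choice is the sponsor's.
2. Use the same wording in the abstract, the primary outcome, the sample size and the data analysis sections, and say which time point the pilot change refers to.
3. Do not use the group main effect averaged over T0 as the fallback.
4. Leave the T0 comparison out of the Bonferroni family, and state how many comparisons the family holds.
5. Apply the same contrast to the nine secondary outcomes, each with its own T0 value.
6. If the pilot data allow, report the level SD and ρ, which would replace the assumed range above.

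**Cost.** Wording, and one or two degrees of freedom. If T0 enters only as a covariate, women with neither T1 nor T2 contribute no data, which sits badly with including all randomised participants. A model that keeps T0 as a response and constrains its mean to be equal in the two groups avoids this. In GEE that version adjusts for T0 only through the working correlation, so an independence structure should not be chosen for it.

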**Methods:**

This study will be a randomized, single-blind, and sham-controlled trial. The study will recruit 76 female patients diagnosed with SUI. They will be randomly allocated to two groups: acupuncture and sham acupuncture, in a 1:1 ratio. Each group of subjects will receive 10 min of acupuncture treatment at RN3 (Zhongji). Outcomes will be assessed at three time points: baseline, during intervention, and 10 min post-intervention, using pelvic floor muscle sEMG. The primary outcome will be the difference in mean amplitude (μV) of the sEMG recordings during the 10-second tonic contraction phase between the acupuncture and sham acupuncture groups. Secondary outcomes will include assessments of amplitude, variation coefficient, and relaxation time across the other phases of the sEMG evaluation. The trial will record adverse events related to the intervention.

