### Randomization

This study was designed as a randomized, sham-controlled trial. The randomization sequence was generated by an independent statistician using a computer-generated random number method (SPSS v26.0; IBM Corp., Armonk, NY, USA). Eligible patients were randomly allocated in a 1:1 ratio to either the acupuncture group or the SA group. The allocation sequence was prepared as sequentially numbered cards and sealed in opaque envelopes bearing corresponding identification numbers. After participants were formally enrolled and completed baseline assessments, an independent researcher not involved in the intervention or outcome assessment opened the envelopes sequentially according to the order of enrollment to obtain the allocation information. The group assignment was then promptly communicated to the acupuncturist responsible for delivering the intervention.

Throughout the study, investigators, outcome assessors, and data analysts will be blinded to group allocation. Strict allocation concealment procedures were implemented to minimize potential selection bias. The study design and reporting adhered to the CONSORT guidelines for randomized controlled trials.

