**Figure 5 F5:**
[figure not shown]
Relationship between SUI, acupuncture, and function of PFM. SUI, stress urinary incontinence; PFM, pelvic floor muscle.

In this study, a single acupoint—RN3 was selected to investigate its acupoint-specific effects while minimizing confounding influences from multi-acupoint interventions. Previous studies support the potential role of RN3 in regulating lower urinary tract function. A case report (11) suggested that acupuncture at RN3 may influence pelvic floor-related functional parameters in the short term, and an experimental study (36) has demonstrated that stimulation at RN3 can modulate bladder activity. According to Traditional Chinese Medicine theory, RN3 is the Front-Mu point of the bladder and a key acupoint of the Ren meridian, with functions in regulating bladder activity and lower urinary tract function (37). From a mechanistic perspective, stimulation of RN3, located in the lower abdomen, may activate afferent nerve fibers, thereby modulating sacral reflex pathways involved in continence control. This neuromodulatory effect may facilitate motor unit recruitment and thereby contribute to the modulation of PFM function.

To ensure both physiological effectiveness and methodological rigor, the intervention duration will be standardized to 10 min. This duration aligns with a prior study (38) on the immediate effects of acupuncture and is considered sufficient to induce and maintain the “Deqi” sensation, which is widely regarded as a prerequisite for therapeutic efficacy (39). Moreover, a controlled and relatively short intervention period helps minimize participant discomfort and reduces potential interference with real-time sEMG recordings, thereby enhancing data reliability. In this study, in order to observe the effect of acupuncture on PFM function, three time points will be set: baseline, during intervention, and 10 min post-intervention. The “during intervention” time point will reflect the changes in PFM function when patients receive acupuncture, aiming to explore the mechanism of acupuncture efficacy. Additionally, the “10 min post-intervention” time point will also include a PFM function assessment to observe the sustained effect of acupuncture on PFM function.

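### When the interaction is not significant, the primary analysis falls back on a group main effect that averages in the pre-allocation value: a diluted estimate and a second route to a positive result

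*Protocol article*

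**What the plan says.** All of this is in the protocol article.

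- **Model (Data analysis).** The relevant sentence opens "For repeated measurements obtained at three time points" and continues "GEE models will be used as the primary analytical approach to account for within-subject correlations". The terms are fixed: "The models will include group, time, and group-by-time interaction terms". T0 is therefore one of the modelled outcomes, and no baseline covariate is named.
- **Decision rule (Data analysis).** "The group-by-time interaction will be examined first; if significant, simple effects analyses will be conducted, otherwise main effects will be interpreted". Bonferroni correction is mentioned next, without saying which comparisons it covers. Tests are two-sided at 0.05.
- **Timing (Randomization).** T0 comes before allocation: "After participants were formally enrolled and completed baseline assessments, an independent researcher not involved in the intervention or outcome assessment opened the envelopes".
- **Outcome (The primary outcome).** "Mean amplitude during the 10-s tonic contraction phase", measured at T0, T1 and T2.
- **Sample size.** The trial is sized on the change in that amplitude: 4.1 (SD 2.7) against 1.9 (SD 1.6) μV, power 0.90, 32 per group, 38 after 15% dropout.
- **Discussion.** The during-intervention "time point will reflect the changes in PFM function when patients receive acupuncture"; the 10-minute value is there to show whether the effect is sustained.

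**The concern.** Testing the interaction first and otherwise reading main effects suits a factorial layout in which every level of time is a post-treatment level. Here one of the three levels precedes randomisation. The expected group difference at T0 is zero by design, so any treatment effect must appear as a group-by-time interaction. If that interaction is not significant, the plan does not stop. It moves to a group main effect that contains the T0 difference, or to a time main effect that does not compare the groups at all.

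Three things are at stake in the primary analysis:

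- The reported quantity is not the change on which the trial was sized.
- A chance imbalance at T0 can be read as a treatment effect.
- A second 5% test is applied to the same primary question after the first has failed.

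**Working it through.** **1. The plan's own figure.** With difference 2.2 = 4.1 − 1.9, SD 2.7 in both arms, two-sided α 0.05 and power 0.90: n = 2(1.960 + 1.282)² × 2.7² / 2.2² = 31.65, so 32 per group. Dropout: 32 / 0.85 = 37.6, so 38 per group and 76 in all. The stated size is reproduced, and it refers to a difference in change.

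**2. What the fallback estimates.** Group main effect = (D0 + D1 + D2) / 3, where Dk is the group difference at Tk and D0 has expectation zero.
- Effect at T1 and T2: (0 + 2.2 + 2.2) / 3 = 1.47 μV, two thirds of the effect.
- Effect at T1 only: (0 + 2.2 + 0) / 3 = 0.73 μV, one third.
- A chance T0 difference enters directly with weight 1/3. Because values within a woman are correlated, part of it also persists in D1 and D2.

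**3. Error under no effect.** If the three values are equally correlated, the mean of the three differences is independent of the interaction contrasts. Two independent 5% tests give 1 − 0.95² = 9.75%. Simulation of the rule used 40,000 trials per setting, 32 or 38 per group, complete data and a small-sample reference distribution. Within-subject correlation ρ is not in the documents and was assumed to be 0.3–0.9.

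| What counts as positive | Total error |
|---|---|
| Significant interaction or main effect | 9.4–9.9% |
| Significant interaction backed by a Bonferroni (three time points) simple effect at T1 or T2, or fallback main effect | 4.9–6.0% |

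The main effect after a non-significant interaction contributes 4.6–4.9 percentage points in both rows. In the second row that is most of the total at ρ = 0.3 (4.8 of 5.9) and nearly all of it at ρ = 0.9 (4.8 of 5.0).

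**4. Where the false positives come from.** Among false-positive fallback results, the share that already had P < 0.05 at T0 is about 35% at ρ = 0.3 and about 75% at ρ = 0.9.

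**5. How often it matters at the design effect.** With 2.2 μV at T1 and T2 and 32 per group, the interaction test has power 0.92 (SD 2.7 in both arms) or 0.98 (SDs 2.7 and 1.6), so the fallback is reached in roughly 2–8% of trials. The main-effect test itself, with SD 2.7 in both arms, has power 0.94, 0.75, 0.45, 0.31 and 0.17 at ρ = 0.3, 0.5, 0.7, 0.8 and 0.9. Hand check at ρ = 0.5: the raw SD is 2.7 / √(2 × 0.5) = 2.7; SE = 2.7 × √((2/3) × (2/32)) = 0.551; 1.467 / 0.551 = 2.66, which gives power of about 0.75.

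**6. After the fix.** For the T0-to-T1 change contrast, SE = 2.7 × √(2/32) = 0.675 and 2.2 / 0.675 = 3.26. Power is about 0.90 by normal approximation and 0.89–0.90 in simulation, whatever ρ is. The average of T1 and T2 minus T0 has power 0.96 if the effect persists. Each has 5% error under no effect.

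**The case against.** The best defence is that the plan tests the right thing first. The interaction is the change contrast, it has high power at the design effect, and the plan says only that main effects will be interpreted, not that they prove efficacy. Effect sizes with 95% CIs are also promised. Part of this stands: at 2.2 μV the fallback is seldom used, and no success rule is written down. It does not rescue the rule, which still tells the analyst to read a quantity that includes a pre-allocation difference.

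A reader might infer three stronger claims that the documents do not support.

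- **The rule doubles the error rate and also loses power.** These belong to different readings. For an assumed smaller effect of 1.1 μV, counting any significant interaction or main effect gives power of 55–78%, no lower than a baseline-adjusted T1 comparison (52–68%), at the price of nearly 10% error. Requiring a Bonferroni-significant simple effect gives 10–69% power, with error of about 5–6%. The protocol does not say which reading applies.
- **Dilution always means a weaker test.** At ρ = 0.3 the main-effect test (0.94) is no weaker than the interaction test (0.92). The loss appears from ρ = 0.5 upward.
- **The error is 11–12%.** Values of that size arise with an uncorrected sandwich variance in small samples. That is a separate matter, and the protocol does not fix the variance estimator.

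Nor is the absence of a named primary time point a fault by itself, since an unseen analysis plan may name one. The fault is the rule that is stated.

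**Conclusion.** The concern holds as a wrongly stated decision rule, not as missing detail. The dilution (2.2 to 1.47 or 0.73 μV) and the mismatch with the change used for sample size follow from the design and need no assumption about correlation. The time main effect is not a treatment comparison under any reading. The second route is real, but its cost depends on what is counted as positive: about 9.5–10% or about 5–6% total error. These totals and the T0-imbalance share rest on an assumed correlation of 0.3–0.9, equal correlation between time points and complete data. The practical harm is mainly in trials with no effect or one smaller than planned.

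**What to change.** Delete the main-effects fallback. Base the primary conclusion on one pre-specified contrast: acupuncture minus sham in mean amplitude of the 10-s tonic phase, with T0 treated as baseline (as a covariate, or through change from T0), at two-sided 0.05, reported with its 95% CI whatever the interaction P value. The interaction can be reported descriptively.

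The sponsor should choose the contrast before unblinding. T1 fits the during-intervention focus; the T1/T2 average has more power if the effect lasts. The Discussion gives both time points a role, so this is the sponsor's decision. If T1 is chosen, T2 becomes secondary or is tested in sequence.

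The cost is a reworded paragraph. No new data are needed and the size stays at 38 per group. The one thing given up is the option of claiming an effect through the main effect.
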